### Statistical analysis

2.6

Statistical analysis will be performed for the total registry population as well as for defined subgroups if applicable. Continuous variables will be presented as mean ± SD or median with interquartile range, and categorical variables (e.g., gender) will be reported as frequencies and percentages. The Kolmogorov–Smirnov test may be used to test for normal distribution. For comparison, χ^2^ test or Fisher's exact test may be used for categorical variables, and *t* test or Mann‐Whitney U test for continuous variables. Linearized rates and actuarial probability statistics may be used where appropriate for adverse event reporting. Kaplan–Meier analysis may be performed for survival and safety outcomes. All statistical analyses will be performed using IBM SPSS Statistics version 24 (IBM, Armonk, New York) or R Core Team (https://www.R-project.org/).

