## INTRODUCTION

1

Transcatheter aortic valve implantation (TAVI) has emerged as standard of care for patients suffering from severe, symptomatic aortic stenosis (AS), irrespective of the level of surgical risk.^1^, ^2^, ^3^, ^4^, ^5^ Since its introduction almost two decades ago,^6^ an evolving understanding of patient and prosthesis selection, increased peri‐procedural expertise, and advances in valve technology have contributed to improved outcomes and patient access to TAVI.^7^

As a consequence of TAVI indications expanding to younger and lower‐risk patients, there has been a clear shift in interest toward reducing healthcare resource utilization, and identifying factors likely to predict potential futility of the procedure^5^, ^8^, ^9^, ^10^ For example, a minimalist approach to help reduce procedure waiting times, resource use and costs, length of hospital stay, and staff workload.^11^, ^12^ Local programs that incorporate procedural algorithms to simplify the TAVI care pathway have been developed by many centers.^8^, ^12^, ^13^, ^14^, ^15^ However, the quality of care (QoC) for TAVI patients across Europe remains highly variable, particularly in terms of effective screening and patient discharge/follow‐up management.^16^, ^17^ A unified strategy is warranted to ensure that all patients receive consistent pre‐, peri‐ and post‐TAVI care and optimized outcomes.^18^

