## METHODS/DESIGN

2

The BENCHMARK registry (ClinicalTrials.gov Identifier: NCT04579445) is a non‐interventional, multicenter, international registry that will enroll patients with severe symptomatic AS undergoing transfemoral (TF) TAVI at 30 centers across Europe (Austria, Czech Republic, France, Germany, Italy, Romania, Spain). Each participating center should have a TAVI coordinator in place. The registry will be conducted according to the European Medical Device Regulations and International Organization for Standardization (ISO 14155:2020) and the ethical principles originating from the Declaration of Helsinki. All participants will provide written informed consent before enrolling in the registry. The protocol and patient informed consent forms will be approved by the local Institutional Review Board (IRB)/Independent Ethics Committee (IEC) at each center prior to initiation of the registry.

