### Study design

2.1

The BENCHMARK registry will document the effect of introducing tailored BENCHMARK QoC measures (Table 1) into TAVI centers using four distinct phases: Retrospective baseline evaluation phase, education phase, implementation phase, and prospective effect documentation phase (Figure 1). For the baseline evaluation phase (retrospective phase), each center will retrospectively document 30 consecutive patients (*N* = 900) undergoing transfemoral TAVI with a balloon expandable transcatheter aortic valve before introducing the BENCHMARK QoC measures. The TAVI procedure and patient discharge within this phase must have been performed prior to the first educational phone call. For each patient, follow‐up data after 1 and 12 months will be recorded. In the education phase, each center will identify a defined leadership team (i.e., multidisciplinary heart team) to undergo online education on the BENCHMARK QoC measures and best practices. A detailed description of the education phase is shown in Figure 2. During the Implementation Phase, consisting of a 2‐month time window, each center will introduce the tailored QoC measures into their hospital routine. Follow‐up calls will be arranged between the BENCHMARK education team and each center every 2 weeks to offer assistance with regard to implementation progress. Finally, each center will prospectively enroll 50 consecutive patients (*N* = 1500) undergoing TAVI after completing the education and implementation phases. This prospective phase is estimated to be 20 months duration overall, with up to 8 months for patient recruitment and 12 months follow‐up for the last patient included.

**TABLE 1 clc23711-tbl-0001:** BENCHMARK QoC measures

BENCHMARK QoC measures	Implementation description
1. Education of patient and family	The patient, and if the patient is not independent, at least one family member or carer is involved in the patient‐education, and discharge provision is discussed with them prior to the procedure.
2. Education and alignment of the internal team (medical and paramedical)	At least one joint meeting per year is organized to educate all staff involved in the diagnostics, post‐procedural care and intervention of patients with severe AS.

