### Patients

2.2

A total number of 2400 patients aged ≥18 years old with symptomatic AS who undergo TF TAVI with a balloon‐expandable transcatheter aortic valve will be included. Approximately 900 consecutive patients will be documented in the retrospective baseline evaluation phase (30 per center) and 1500 patients in the prospective phase (50 per center). The sample size estimate is based on the ability to discriminate any changes in outcomes between the retrospective baseline evaluation phase and the prospective effect documentation phase.

All patients irrespective of transcatheter valve type or access route, will be documented in an electronic case report form (eCRF) based patient logbook. A defined core data set will be collected for all patients (mortality, stroke, time of discharge/length of hospital stay, readmission).

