### Registry objectives

2.5

The primary objective of the BENCHMARK registry is to document the effect of introducing tailored BENCHMARK QoC measures into TAVI centers to (1) decrease length of hospital stay; and (2) reduce the need for ICU capacity. Secondary objectives will be to streamline diagnostics, minimize staff workload allowing timely delegation of responsibilities, ascertain uncompromised patient safety post‐TAVI (VARC‐2 defined early and time‐related valve safety), improve patient quality of life (QoL), patient and staff satisfaction, and improve the implementation of BENCHMARK QoC measures by each center over time. A full description of the primary and secondary objectives of the BENCHMARK registry is provided in Table 4.

**TABLE 4 clc23711-tbl-0004:** BENCHMARK registry objectives

Primary objectives	
Reduction in length of hospital stay	To reduce the length of hospital stay (door to needle, needle to door, overall stay) in order to reduce overall costs based on hospitalization, and to enable early return to normal life: Separate single hospitalization for diagnostics Door to needle (days) Needle to door (days) Timely discharge to home, rehabilitation center or other institution Economic effect assessment associated with hospitalization changes after implementation of BENCHMARK QoC measures
Reduction of the need for ICU capacity	To accelerate the post‐procedural patient care recovery pathway: Minimize/eliminate time spent in the recovery room, ICU, CCU or IMC and prioritize a rapid return to general ward, in order to reduce the level of invasiveness of post procedural care (e.g., with regard to COVID‐19): Time spent in the recovery room (hours) Time spent on the ICU (hours) Time spent on the CCU (CCU) (hours) Time spent on the IMC (hours/days) Time spent on the general ward (hours/days)

Secondary objectives	
Streamlining of diagnostic and procedural times	To streamline diagnostics to avoid duplication of diagnostic measures and to tighten schedules: Proportion of repeated diagnostic procedures Patient status assessment: physician versus nurse/coordinator To reduce the procedural time without compromising patient safety post TAVI: Time between incision and sheath removal (min) Time between entering and leaving the OR/catheterization laboratory/hybrid room (min)

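### The only tests named for comparing phases assume independent patients, although the measures are introduced by centre and the same 30 centres supply both phases

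*Protocol article*

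**What the plan says.** The registry runs "at 30 centers across Europe (Austria, Czech Republic, France, Germany, Italy, Romania, Spain"). Section 2.1 (Study design) makes the centre the unit that receives the intervention: "each center will introduce the tailored QoC measures into their hospital routine". The same centres supply both sides of the comparison. In the baseline phase "each center will retrospectively document 30 consecutive patients", and after education and implementation "each center will prospectively enroll 50 consecutive patients". Section 2.2 (Patients) bases the sample size on detecting change between these two phases.

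The primary objective in section 2.5 is to document the effect of the measures to (1) "decrease length of hospital stay; and (2) reduce the need for ICU capacity". For comparisons, section 2.6 offers the chi-square test or Fisher's "exact test may be used for categorical variables, and *t* test or Mann‐Whitney U test for continuous variables". It names no centre effect, stratification, mixed model or cluster-robust variance. It also gives no alpha, plans no confidence interval and designates no primary analysis. Section 3.2 (Potential limitations) mentions variation between and within countries and limited scope for adjustment, but not the clustering of patients in centres.

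**The concern.** Two parts of the between-centre variation matter, and they act in opposite directions.

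- **Stable differences in level.** A centre with long stays before tends to have long stays after. Each centre is its own control, so this part cancels from the before-after difference. A two-sample test leaves it in the error term and is then too conservative.
- **Differences in change.** If some centres shorten stays more than others, or drift for local reasons, the average change is estimated from 30 centre-level changes. It does not rest on 2400 independent patients. A two-sample test leaves this part out of the standard error and is then too liberal.

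The Introduction says that "the quality of care (QoC) for TAVI patients across Europe remains highly variable", which speaks to differences in level. Differences in change are plausible for another reason: Table 4 has implementation of the eight measures rated from 0% to 100% per centre over time, so uptake may well differ. At stake is whether p-values for length of stay, ICU time and the safety outcomes mean what they appear to mean.

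**Working it through.** **Inputs from the document.** Centres C = 30; patients per centre m1 = 30 before and m2 = 50 after (sections 2.1 and 2.2).

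**Headcount.** 30 × 30 = 900 and 30 × 50 = 1500, in total 2400, as stated. There is no power or precision figure to reproduce, because alpha, power, effect size and SD are not given.

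**Assumptions.** Two-sided 5% test; ICC (share of the total variance that lies between centres) 0.01 to 0.20; CAC (correlation of a centre's two true phase means) 0.5 to 1.0. None of these is in the document.

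**Formulas**, with total variance set to 1 and h = 1/30 + 1/50 = 0.05333:

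- Variance of the phase difference if patients are independent: h/30 = 1/900 + 1/1500 = 0.00178.
- Variance with centre effects: [(1 − ICC)·h + 2·ICC·(1 − CAC)]/30.
- Variance ratio: VR = (1 − ICC) + 2·ICC·(1 − CAC)/h = (1 − ICC) + 37.5·ICC·(1 − CAC).
- Actual type I error: 2·[1 − Φ(1.96/√VR)].

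**Worked case**, ICC 0.10 and CAC 0.8: VR = 0.90 + 37.5 × 0.10 × 0.2 = 1.65. The true standard error is √1.65 = 1.28 times the naive one. Then 1.96/1.28 = 1.53, and the type I error is 12.7%.

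| ICC | CAC | VR | True SE / naive SE | Actual type I error |
|---|---|---|---|---|
| 0.01 | 1.0 | 0.99 | 0.995 | 4.9% |
| 0.01 | 0.5 | 1.18 | 1.09 | 7.1% |
| 0.05 | 1.0 | 0.95 | 0.97 | 4.4% |
| 0.05 | 0.9 | 1.14 | 1.07 | 6.6% |
| 0.05 | 0.8 | 1.33 | 1.15 | 8.9% |
| 0.10 | 1.0 | 0.90 | 0.95 | 3.9% |
| 0.10 | 0.9 | 1.28 | 1.13 | 8.3% |
| 0.10 | 0.8 | 1.65 | 1.28 | 12.7% |
| 0.10 | 0.5 | 2.78 | 1.67 | 23.9% |
| 0.20 | 1.0 | 0.80 | 0.89 | 2.8% |
| 0.20 | 0.9 | 1.55 | 1.24 | 11.5% |
| 0.20 | 0.8 | 2.30 | 1.52 | 19.6% |

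**Break-even.** VR = 1 when 37.5·(1 − CAC) = 1, that is CAC = 1 − h/2 = 0.973, whatever the ICC. Below that value the pooled test is too liberal; above it, too conservative.

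**Simulation** (normal outcomes, 20,000 registries per setting). The pooled t test rejected in 4.0% (ICC 0.10/CAC 1.0), 12.7% (0.10/0.8) and 6.7% (0.05/0.9). A paired t test on the 30 centre-level differences rejected in 5.0%, 4.9% and 5.1%.

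The calculation is for means. Skewed stays and ICU times would change the figures but not the principle. The usual parallel-cluster design effect, 1 + (m − 1)·ICC, does not apply, because every centre appears in both phases in the same 3:5 ratio.

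**The case against.** The strongest reply is that section 2.6 is a permissive list in a condensed article. Each comparison method is one that may be used, none is designated as primary, and a full analysis plan that is not shown may already include centre. This stands in part: the article does not bind the registry to a pooled test. It does not dispose of the point, because the article goes beyond silence. It names specific methods, every one of them ignores centre, and it does not refer the reader elsewhere for the comparison.

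Second, the size and even the direction of the error are unknown. That is correct. With stable centre effects, or an ICC near 0.01, the harm is small or the test is conservative. Variable care between centres, as the Introduction describes it, shows differences in level and does not by itself show differences in change.

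Third, the registry is non-interventional, and its limitations section already admits confounding and limited adjustment. But accounting for centre is possible with data that the design yields, and non-randomisation does not stand in its way.

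A reader might also infer more than the text supports:

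- **Wrong confidence intervals.** Section 2.6 plans none.
- **A normality test that forces a rank test and so loses the days saved.** The Kolmogorov–Smirnov test is only mentioned as a possible check, and the text does not say that it selects the method. Means or medians are to be reported in any case.
- **Centre confounded with phase.** The plan is for patients "documented in the retrospective baseline evaluation phase (30 per center) and 1500 patients in the prospective phase (50 per center"), which balances centre across phases. Imbalance would arise only if centres missed these quotas, and the document does not say that they will.

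**Conclusion.** The point holds as a defect in the methods named. For a before-after comparison in the same 30 centres, with the measures introduced by centre, independent-sample tests do not give valid p-values in general.

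Over ICC 0.05 to 0.10 and CAC 0.8 to 0.9, a nominal 5% test has an actual size of 6.6% to 12.7%. It reaches 19.6% at 0.20/0.8, falls to 3.9% at 0.10/1.0, and lies between 4.9% and 7.1% at ICC 0.01. Every one of these figures rests on assumed ICC, CAC and alpha.

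The liberal direction is the more plausible one. It needs only a CAC below 0.973, and uptake of eight measures that centres introduce themselves may easily differ that much. The documents do not show that inflation is certain, or how large it will be.

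**What to change.** In section 2.6, replace the two-sample tests for the between-phase comparisons of length of stay, ICU time and the binary safety outcomes by an analysis that accounts for centre and for centre-by-phase variation. Either of these would do:

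- A mixed model with phase as fixed effect and random centre and centre-by-phase effects, logistic for binary outcomes. For ICU time the distribution must allow zeros, since Table 4 aims to minimise or eliminate that time. A plain gamma model would therefore not serve.
- A paired analysis of the 30 centre-level differences, which estimates days saved directly.

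The two are not interchangeable: a log-link model estimates a ratio, the paired analysis a difference. The choice should be made in advance, and the effect reported with a 95% confidence interval. If the full plan already handles centre, a sentence in the article saying so is enough.

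The cost is wording only. Patients are already recorded by centre, and R is already named as software. The downside is that intervals may be wider than the naive ones: by a factor of about 1.28 at ICC 0.10/CAC 0.8, but slightly narrower (0.95) if centre effects are fully stable.

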## DISCUSSION

3

The BENCHMARK registry has been designed to document the effect of introducing tailored BENCHMARK QoC measures into TAVI centers. Analysis of the data gathered may provide additional insights to further refine and improve QoC measures and best practices for the effective management of patients with severe AS. The knowledge acquired from the BENCHMARK registry dataset will help to standardize care pathways and treatment outcomes for TAVI patients across Europe.

### Studies that support the BENCHMARK registry

3.1

Results from the European FAST‐TAVI study support the BENCHMARK registry and show that the use of a pre‐defined set of QoC measures can lead to reduced use of medical resources, improved QoL, and optimized patient outcomes.^21^, ^22^ FAST‐TAVI is a real‐world, observational, prospective trial designed to assess early discharge feasibility and safety after transfemoral TAVI (TF‐TAVI).^22^ Patients (*N* = 502) with severe AS scheduled to undergo TF‐TAVI with a balloon‐expandable transcatheter heart valve were enrolled from ten sites in Italy, the Netherlands, and the United Kingdom.^22^ FAST‐TAVI provides evidence that close monitoring, early mobilization and accelerated reconditioning, and discharge planning should be included in the TAVI program since these are important aspects of QoC.^19^ By adhering to the FAST‐TAVI discharge criteria, patients that were appropriately discharged early had a lower risk of TF‐TAVI‐related complications, such as all‐cause mortality, vascular complications (0.3% vs. 4.7%; *p* = .004), permanent pacemaker implantation (4.3% vs. 15.9%; *p* < .001), stroke (0.0% vs. 2.8%), and major bleeding at 30 days (0.3% vs. 6.5%; *p* < .001).^22^ The primary endpoint (a composite of all‐cause mortality, vascular access–related complications, permanent pacemaker implantation, stroke, cardiac rehospitalization, kidney failure, and major bleeding) was reached in 27% of patients (95% confidence interval [CI]: 23.3, 31.2) within 1‐year post‐procedure.^16^ Moreover, only 7.5% (95% CI: 5.5, 10.2) had in‐hospital complications before discharge and 19.6% (95% CI: 16.3, 23.4) within 1 year after discharge.^16^ This study highlights that adoption of simple, standardized TAVI‐specific QoC measures can help select patients for early discharge without impacting on clinical outcome.^21^, ^22^

The results of the European FAST‐TAVI project are supported by the outcomes of the French FAST‐TAVI 1 study,^13^, ^14^ which is a prospectively assess the feasibility and safety of within 72 hours discharge after transfemoral TAVI. Patients were prospectively assessed for early discharge home. Death or repeat hospitalization within 30 days occurred in 4 cases (5%) among patients discharged early. Factors associated with delayed discharge were blood transfusion (HR 13.85, 95% CI 1.61–119.40) and pacemaker implantation (HR 4.47, 95% CI 1.34–14.26). The authors confirmed the conclusion of the European FAST‐TAVI in that early discharge is safe and attainable in a large proportion of patients. The follow‐up study, FAST‐TAVI 2, is currently ongoing.

Data from the Vancouver 3M TAVR study also provides evidence that the BENCHMARK registry is feasible.^17^ Vancouver 3M is a prospective, multicenter study to document the efficacy, feasibility, and next‐day discharge of patients undergoing contemporary balloon‐expandable transfemoral TAVR using the minimalist Vancouver 3M Clinical Pathway approach. This clinical pathway was created to standardize TAVR care and reduce hospital stay length in a selected patient group; it includes measures such as risk‐stratified periprocedural practices, post‐procedure care, and a criteria‐driven discharge algorithm.^17^ Patients were screened (*N* = 1400) at 13 low‐, medium‐, and high‐volume North American centers between March 2015 and April 2017, of which 411 were enrolled with a median age of 84 years.^17^ The Vancouver 3M TAVR study results also demonstrated that a streamlined TAVI pathway allows for next‐day discharge home, with reproducible efficacy and safety outcomes.^17^ The composite primary endpoint of all‐cause mortality or stroke by 30 days occurred in 2.9% (95% CI: 1.7%, 5.1%) of patients.^17^ Notably, 80.1% of the elderly patients achieved next‐day discharge home, of which 89.5% were discharged home within 48 hours post‐procedure.^17^

Such is the importance of standardizing and streamlining care associated with the TAVI procedure that other countries and centers are reviewing possible initiatives, including the Canadian Cardiovascular Society Quality Initiative, the TAVI Care and Cure program developed in Rotterdam, and the European IMPULSE registry.^28^, ^29^, ^30^, ^31^ In addition, the guidelines from the European Society of Cardiology and the European Association for Cardio‐Thoracic Surgery support the QoC initiatives for patients undergoing TAVI, with the focus on patients being treated at heart valve centers/centers of excellence to deliver the best QoC for patients.^5^

The BENCHMARK registry will further support the findings from these studies, and determine potential cost savings and improvements in QoC that can be adopted as the new benchmark.

### Potential limitations

3.2

The BENCHMARK registry will be conducted in multiple centers in seven European countries, which increases the applicability of findings but might limit the generalizability of the results across wider territories. Furthermore, not all patients having TAVI will be eligible for this registry. It is important to consider that inter‐ and intra‐country variation in healthcare systems and resources may have an unintended impact on the registry dataset. Due to the lack of central adjudication of safety events, the assessment of endpoints may be inconsistent between centers. This registry is not randomized and, as a result, there is the potential for confounding and bias in the analysis with limited ability for adjustment. In addition, we expect that length of stay will also decline in hospitals in general, but probably to a lesser extent. However, it is hoped that implementing standardized BENCHMARK QoC measures will minimize any bias owing to possible differences in healthcare systems.

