### Data collection

2.4

Clinical outcome data collected will be based on the center's standard of care for TAVI. Data will be collected according to the timetable set out in Table 3, and include physical assessments, medical history and symptoms, diagnostics, electrocardiography (ECG), echocardiography (Echo), hospitalization and procedural duration, safety parameters, QoL measures, satisfaction surveys, as well as resource utilization parameters. Data will be captured in an eCRF by either a study nurse or physician, and the registry sponsor will check all data for plausibility and completeness.

**TABLE 3 clc23711-tbl-0003:** Data collection schedule

	Baseline evaluation phase (retrospective documentation phase)					Effect documentation of BENCHMARK QoC measures (prospective enrollment phase)				
	Screening/baseline	TAVI	Discharge	30 days visit *Visit or call* (±1 week)	12 months visit *Visit or call* (±3 weeks)	Screening/baseline	TAVI	Discharge	30 days visit (±1 week)	12 months visit (±3 weeks)
Signed informed consent	X^a^					X^b^				
Inclusion/exclusion criteria	X					X				
Referral management	X					X				
Treatment decision	X					X				
Tasks, being impacted by the coordinator								X		
Demographics	X					X				
ECG and Echo	X	X	X	X^c^	X^c^	X	X	X	X	X
Comorbidities	X					X				
Symptoms and social characteristics	X					X				
Risk score (Euro Score II)	X					X				
Frailty, mental, social status	X					X				
Quality of life (TASQ)						X		X	X	X
Procedural details (device success)		X					X			
Length of hospital stay			X					X		
Safety and efficacy variables (VARC‐2)^27^			X	X	X			X	X	X
Rehospitalization data				X	X				X	X
Adverse event reporting		X	X	X	X		X	X	X	X
BENCHMARK QoC measures (center and patient based)								X		
Patient/physician/coordinator/nursing staff satisfaction			X^d^					X		
Self‐reported working hours per patient (physician, coordinator, nursing staff)								X		

Abbreviations: ECG, electrocardiogram; Echo, echocardiogram; IRB, institutional review board; TAVI, transcatheter aortic valve implantation; QoC, quality of care; TASQ, Toronto Aortic Stenosis Quality of Life Questionnaire; VARC‐2, Valve Academic Research Consortium‐2 consensus document.

^a^
The TAVI and discharge visits of patients being eligible for retrospective documentation must have been documented prior to site's education on BENCHMARK QoC measures. Need for consent form according to local IRB requirements.

^b^
Consent needs to be given prior to the TAVI procedure.

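### The named phase comparison is unadjusted, while the protocol expects length of stay to fall anyway; the difference estimates programme effect plus background decline

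*Protocol article*

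**What the plan says.** - **Objective.** Section 2.5 (Registry objectives) says the primary aim "is to document the effect of introducing tailored BENCHMARK QoC measures into TAVI centers", with shorter hospital stay and less need for ICU capacity as the two targets.
- **Contrast.** In section 2.1 (Study design), "each center will retrospectively document 30 consecutive patients" treated before the education phase. After education and a 2-month implementation window, each centre enrols 50 further patients. Section 2.2 (Patients) bases the sample size on the ability "to discriminate any changes in outcomes between the retrospective baseline evaluation phase and the prospective effect documentation phase". No concurrent control is described.
- **Analysis.** For comparisons, section 2.6 (Statistical analysis) names the chi-square or Fisher test for categorical variables and the t "test or Mann‐Whitney U test for continuous variables". Kaplan–Meier analysis is optional. No covariate, centre or calendar-time term is mentioned, and the wording is permissive throughout.
- **Expected bias.** Section 3.2 (Potential limitations) says "there is the potential for confounding and bias in the analysis with limited ability for adjustment" and adds "we expect that length of stay will also decline in hospitals in general, but probably to a lesser extent". The remedy it offers is the hope that standardised measures will reduce bias from differences between healthcare systems.
- **Available covariates.** Table 3 schedules demographics, comorbidities, EuroSCORE II and frailty, mental and social status in both phases.

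**The concern.** All baseline patients at a centre are treated before all of its prospective patients. Anything that shortens stay over calendar time therefore enters the phase difference with the same sign as a programme benefit. The authors expect such a decline. The tests named in section 2.6 cannot separate it from the programme, and more patients do not help, because the bias equals the whole background decline at any sample size. The remedy in section 3.2 concerns variation between healthcare systems, not a trend over time.

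Case mix may add to this. The Introduction describes TAVI expanding to younger and lower-risk patients, and section 2.3 excludes largely incomplete records in the baseline phase only. The article does not show that risk will differ between these two phases, so this part is a possibility.

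At stake is the headline reading. A difference that includes the general trend could be reported as what the measures achieved, and the Discussion intends to carry the findings into cost savings and a new standard of care.

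**Working it through.** **1. The plan's own figure.** 30 centres × 30 = 900 baseline patients; 30 × 50 = 1500 prospective patients; 900 + 1500 = 2400, as stated. The article gives no alpha, power, SD or target difference, so there is no power calculation to reproduce.

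**2. Precision of the unadjusted comparison** (centre clustering ignored). In SD units, SE = √(1/900 + 1/1500) = 0.0422. The difference detectable with 80% power at two-sided 5% is (1.960 + 0.842) × 0.0422 = 0.118 SD, so small drifts matter.

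**3. Time between phases (assumed).** Fifty patients in 8 months, the upper limit in section 2.1, is 6.25 per month, so 30 patients take 30/6.25 = 4.8 months. Education plus implementation is taken as 3 months, of which the article gives 2 for implementation. Midpoint gap = 4.8/2 + 3 + 8/2 = 9.4 months.

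**4. Chance of a significant reduction with zero programme effect.** For a background decline r per year and log length-of-stay SD s:

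- shift on the log scale: L = −ln(1 − r) × 9.4/12
- probability = 1 − Φ(1.96 − L/(s × 0.0422))

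Example, r = 5% and s = 0.6: L = 0.0513 × 0.783 = 0.0402; 0.0402/(0.6 × 0.0422) = 1.59; 1 − Φ(0.37) = 36%.

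| Decline per year | L | s = 0.5 | s = 0.6 | s = 0.8 |
|---|---|---|---|---|
| 3% | 0.0239 | 20% | 15% | 11% |
| 5% | 0.0402 | 48% | 36% | 22% |
| 8% | 0.0653 | 87% | 73% | 49% |
| 10% | 0.0825 | 97% | 90% | 69% |

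The nominal rate in this direction is 2.5%. The probability passes 50% at a decline of about 5.1%, 6.1% or 8.1% per year for s = 0.5, 0.6 or 0.8.

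**5. Cross-check without the timing assumption.** A drift of 0.05, 0.10 or 0.15 SD between phases gives 22%, 66% or about 95%.

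**6. Price of a calendar-time term.** With evenly spaced procedures (30 over months 0 to 4.8, 50 over months 7.8 to 15.8), the correlation of phase with time is 0.911. The variance inflation factor is 1/(1 − 0.911²) ≈ 5.9, so the SE of the phase effect is about √5.9 = 2.4 times larger. For a true 10% reduction at s = 0.6, the effect is 0.1054/0.6 = 0.176 SD. Power is 1 − Φ(1.96 − 0.176/0.0422) ≈ 99% without the time term and 1 − Φ(1.96 − 0.176/(2.4 × 0.0422)) ≈ 41% with it.

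**The case against.** Four arguments on the other side deserve weight.

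- **The article condenses a fuller plan.** The tests are introduced with "may", and limited ability to adjust implies some adjustment. A reader might infer that the sponsor has decided against adjusting; the text does not say so. What stands is narrower: every comparison method actually named is unadjusted, next to an expected bias that such methods cannot remove.
- **The limitation is disclosed.** That is to the authors' credit, and the registry sets no alpha or formal hypothesis. But disclosure does not separate trend from programme, and the objective is still worded as an effect.
- **The size is uncertain.** A reader might infer that significance is likely even if the measures do nothing. The calculation does not support that: at 3% or 5% per year the probability stays below one half for every SD shown, and at 8% it straddles one half. Nor does the article imply that there is no programme effect, since the authors expect the general decline to be smaller.
- **Adjustment has limits.** The Introduction's remark on lower-risk patients is about TAVI in general, so a case-mix shift between these phases is not established. Table 3 ticks the same covariate rows in both phases, but baseline values are collected retrospectively and frailty in particular may be recorded less well. Covariates also do nothing about a time trend.

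The last two points temper the claim and the remedy. None removes the mismatch between objective and stated comparison.

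**Conclusion.** The concern holds. By the protocol's own expectation, the stated phase comparison estimates the effect of the measures plus the general decline in length of stay, and possibly case-mix differences. Depending on assumptions, the chance that background decline alone yields a significant reduction runs from about 11% (3% per year, log SD 0.8) to 97% (10% per year, log SD 0.5), against a nominal 2.5%. These figures rest on an assumed 9.4-month gap, assumed SDs and decline rates, no programme effect, and no allowance for clustering. The direction of the bias follows from the text; its size cannot be fixed from it. The supportable statement is that false attribution is possible and well above the nominal rate.

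**What to change.** 1. **Primary estimate.** Estimate the phase effect with a regression model that includes centre and adjusts for EuroSCORE II, age, sex and frailty, which Table 3 schedules in both phases. State that the baseline values are retrospective and that this addresses measured case mix only.
2. **Sensitivity analysis.** Prespecify, and report beside it, the same model with one common linear term for the procedure date. Under the assumed timing the SE is about 2.4 times larger, and an effect that builds up gradually during enrolment would be partly absorbed by the slope.
3. **Wording.** Describe the main result as a before-after change that includes any secular trend, not as the effect of the measures alone. Do not make attribution hinge on significance in the calendar-time analysis: a true 10% reduction would pass that test only about 40% of the time (log SD 0.6).

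The cost is analysis and reporting text, with no new data. The price is a more modest claim and a wide interval in the sensitivity analysis.
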